## Abstract

**Background:**

Following surgery for soft tissue sarcoma of the retroperitoneum, the predominant pattern of failure is local recurrence, which remains the main cause of death. Radiotherapy is utilized to reduce recurrence rates but the efficacy of this strategy has not been definitely established. As treatment tolerability is more favorable with preoperative radiotherapy, normofractionated neoadjuvant treatment is the current approach. The final results of the prospective, randomized STRASS (EORTC 62092) trial, which compared the efficacy of this combined treatment to that of surgery alone, are still awaited; preliminary results presented at the 2019 ASCO Annual Meeting indicated that combined treatment is associated with better local control in patients with liposarcoma (74.5% of the cohort, 11% benefit in abdominal progression free survival after 3 years, *p* = 0.049). Particles allow better sparing of surrounding tissues at risk, e.g., bowel epithelium, and carbon ions additionally offer biologic advantages and are preferred in slow growing tumors. Furthermore, hypofractionation allows for a significantly shorter treatment interval with a lower risk of progression during radiotherapy.

**Methods and design:**

We present a prospective, randomized, monocentric phase II trial. Patients with resectable or marginally resectable, histologically confirmed soft tissue sarcoma of the retroperitoneum will be randomized between neoadjuvant proton or neoadjuvant carbon ion radiotherapy in active scanning beam application technique (39 Gy [relative biological effectiveness, RBE] in 13 fractions [5–6 fractions per week] in each arm). The primary objective is the safety and feasibility based on the proportion of grade 3–5 toxicity (CTCAE, version 5.0) in the first 12 months after surgery or discontinuation of treatment for any reason related to the treatment. Local control, local progression-free survival, disease-free survival, overall survival, and quality of life are the secondary endpoints of the study.

**Discussion:**

The aim of this study is to confirm that hypofractionated, accelerated preoperative radiotherapy is safe and feasible. The rationale for the use of particle therapy is the potential for reduced toxicity. The data will lay the groundwork for a randomized phase III trial comparing hypofractionated proton and carbon ion irradiation with regard to local control.

**Trial registration:**

ClinicalTrials.gov NCT04219202. Retrospectively registered on January 6, 2020

## Background

Retroperitoneal sarcomas constitute approximately 15% of all soft tissue sarcomas [1, 2]. As the early stages can remain without specific signs or symptoms for a long time, many patients are often diagnosed with large tumors. The main histology is lipo- or leiomyosarcoma and about 60% are high-grade tumors [3]. The primary treatment of patients with retroperitoneal sarcomas is surgery; however, the close proximity to intraabdominal organs hinders resections with wide margins in many cases and about 45% of tumors are resected incompletely (R1/R2) [4]. The risk of local failure is generally high especially when a complete resection cannot be achieved. The general policy for local recurrence is re-operation. Retroperitoneal sarcomas show a lower risk for distant metastases; local control is crucial as the primary cause of death in these patients is local disease recurrence [4–6]. In contrast to extremity sarcomas, most patients die without distant metastases. Preoperative radiotherapy seems to be able to reduce the risk of local recurrence based on data from small sample sized studies and retrospective analyses [1]; at many centers, external beam radiotherapy is combined with an intraoperative radiotherapy [7]. The final publication from the only prospective trial comparing surgery with or without neoadjuvant conventional photon radiotherapy is still awaited. Until now, the role of radiotherapy is substantiated on the role in extremity sarcoma. The toxicity of a preoperative treatment is significantly lower compared to a postoperative treatment; however, the potential for toxicity is significant based on the typically large tumor volumes and precise radiation techniques are required. The special physical and biological properties of protons and carbon ions lead to a superior dose distribution [8, 9]. This allows a better sparing of the surrounding organs at risk, with chances to reduce treatment-related side effects and even potential for dose escalation. Considering the typically large target volumes, reduced dose to the surrounding bowel, kidney, and the hematopoietic tissue in the bone marrow is particularly desirable. Primary phase I data for neoadjuvant proton radiotherapy show promising results with mild toxicity [10]. Additional carbon ions have a higher biological effectiveness and are promising in the treatment of sarcoma and chordoma. The standard neoajuvant normofractionated radiotherapy consists of 25 fractions with 2-Gy single dose over 5 weeks; the special properties of particles allow hypofractionation resulting in a reduced treatment total time of 3 weeks.

Herein we present a single-institution, prospective, randomized trial for a neoadjuvant hypofractionated carbon ion or proton radiotherapy of retroperitoneal sarcoma.

## Methods and design

### Primary objective

The primary objective of this trial is the evaluation of safety and feasibility of neoadjuvant hypofractionated irradiation in patients with retroperitoneal sarcoma using ions (protons or carbon ions) in raster scan technique. The primary endpoint is defined as the proportion of patients treated without grade 3–5 toxicity (CTCAE) up to 12 months after treatment and without discontinuation of the treatment for any reason.

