### Toxicity, safety, and quality of life

Toxicity will be evaluated according to International Common Terminology Criteria for Adverse Events (CTCAE) version 5.0 for toxicity (case report forms) and adverse event reporting including the results of clinical examinations as well as imaging studies (MRI or CT). At enrollment, each patient will pass a baseline clinical examination. During treatment, the patient is monitored continuously and acute adverse events will be documented weekly and at the end of treatment. Three weeks after the end of radiotherapy, the patient will receive an MRI, and the surgery is planned 4–6 weeks after RT. The further follow-up presentations are 6 weeks and 3, 6, 9, and 12 months after the tumor resection and include all imaging studies (CT/MRI) (Table 1). The criteria for feasibility and safety are fulfilled, if no grade 3 or higher toxicity has occurred from the start of irradiation until 12 months after surgery, and if the therapy was not canceled due to any reason (unless clearly not treatment related).

**Table 1 Tab1:** Time flow of procedures and examinations

	Study inclusion	Prior to RT	During RT	At the end of RT	3 weeks after RT	OP: 4–6 weeks after RT	6 weeks after RT	3 months after OP	6 months after OP	9 months after OP	12 months after OP
Inclusion and exclusion criteria	x										
Informed consent	x										
Medical history	x		x	x	x		x	x	x	x	x
Evaluation of symptoms and toxicity	x		x	x	x		x	x	x	x	x
Radiotherapy			x								
Resection						x					
MRI abdomen/pelvis		x			x			x	x	x	x
CT thorax		x						x	x	x	x
Quality of life (QLQ-C30)		x			x			x			x

Quality of life (QoL) will be assessed by the means of the EORTC QLQ-C30 questionnaires. Those will be filled out by the patient before treatment, 3 weeks after the end of RT, 6 months after surgery, and at the end of the observation interval of 12 months. The evaluation will be carried out after the complete acquisition of data. Changes in QoL will be determined comparing the results before and after radiotherapy as well as the difference before and after surgery. QoL will be compared between the two arms of the study after the end of radiation and at the end of the observation interval.

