### Statistical consideration and analysis

This study is performed to deliver basic data for the neoadjuvant hypofractionated carbon ion or proton radiation treatment of patients with retroperitoneal soft tissue sarcoma by providing safety and toxicity data for the here presented treatment regimen. The standard treatment is a neoadjuvant normofractionated photon radiotherapy and is considered as the historical cohort which served for the planning of this pilot study including the framework of the safety and feasibility considerations. The randomization will be performed as block randomization at a ratio of 1:1 aiming at equal group sizes by using a web-based randomization tool (randomizer.at).

The primary endpoint is assessed by calculating the two-sided 95% Agresti–Coull interval [13] for each treatment group. The considerations on the choice of the sample size are based on this analysis approach. It is assumed that the proportion of patients treated without grade 3–5 toxicity (CTCAE) up to 12 months after treatment and/or without discontinuation of the treatment for any reason is 0.90. The lower boundary of the two-sided 95% confidence interval should then not fall below 0.75. To achieve this goal under the above assumption, *n* = 32 patients per arm are required.

The intention-to-treat population (ITT) is the primary population for the primary and secondary endpoints and consists of all patients who were included in the study and were treated at least once. The per-protocol population consists of all patients who obtained the allocated treatment as planned and whose documentation is complete. The safety population includes those patients who started treatment (at least 1 day); this is the primary cohort for the analysis of all safety variables.

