### Regular study end

The estimated period of patient accrual is 4 years. The regular end of the treatment period for each patient is 2 to 3 weeks after initiation of radiation therapy (13 fractions, 5–6 fractions per week). The regular end of study participation for each patient is after a follow-up period of 12 months after surgery.

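### The primary endpoint is worded inconsistently (which discontinuations count, 'and' versus 'and/or', time window), so the same patient can be a success or a failure

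*Protocol article*

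**What the plan says.** The protocol article describes the primary endpoint in four places.

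- **Primary objective** (the formal definition): the proportion of patients without grade 3–5 toxicity "up to 12 months after treatment and without discontinuation of the treatment for any reason". Both components are required, and every discontinuation counts.
- **Toxicity, safety, and quality of life** (criteria for safety and feasibility): the toxicity component reads "no grade 3 or higher toxicity has occurred from the start of irradiation until 12 months after surgery". A second component, also required, makes a cancelled therapy a failure, but it exempts cancellations for which a link to the treatment can clearly be ruled out.
- **Statistical consideration and analysis** (the sample-size assumption): the proportion without grade 3–5 toxicity "up to 12 months after treatment and/or without discontinuation of the treatment for any reason is 0.90". Window and discontinuation rule match the Primary objective; the connective does not.
- **Abstract, Methods and design** (worded as the failure event): grade 3–5 toxicity "in the first 12 months after surgery or discontinuation of treatment for any reason related to the treatment".

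Two further statements bear on the window. Regular study end says "The regular end of the treatment period for each patient is 2 to 3 weeks after initiation of radiation therapy", which ties treatment to radiotherapy. The toxicity section says "the surgery is planned 4–6 weeks after RT". Nothing in the article says which wording governs.

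**The concern.** This is not detail left for a fuller document. The article states the endpoint repeatedly, and the statements do not agree. An analyst who follows one section exactly will classify some patients differently from an analyst who follows another.

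The affected patients stay in the analysis, because the intention-to-treat set is everyone included and treated at least once. The results are meant to support a phase III trial. The observed proportion cannot be interpreted, or set against the assumed 0.90, until the event being counted is fixed.

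**Working it through.** **1. The wordings side by side**

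| Place | Window for toxicity | Discontinuation that counts as failure | Link |
|---|---|---|---|
| Primary objective | to 12 months after treatment | any reason | and |
| Toxicity section | start of irradiation to 12 months after surgery | any, unless clearly unrelated | and |
| Statistical section | to 12 months after treatment | any reason | and/or |
| Abstract (failure event) | first 12 months after surgery | related to treatment only | or |

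The abstract's 'or' is not a conflict. Failing if either event occurs is the complement of succeeding only if neither does. The conflict in the connective is the statistical section against the Primary objective and toxicity sections.

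**2. The same patient under each wording**

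| Patient | Primary objective | Toxicity section | Statistical section, 'or' reading | Abstract, literal |
|---|---|---|---|---|
| A. Stops radiotherapy for a clearly unrelated reason, no grade 3–5 toxicity | failure | success | success | success |
| B. Grade 3 toxicity before surgery only, radiotherapy completed | failure | failure | success | success |
| C. First grade 3 toxicity in the last 4–6 weeks before month 12 after surgery, radiotherapy completed | success* | failure | success | failure |
| D. Grade 3–5 toxicity inside every window, radiotherapy completed | failure | failure | success | failure |

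*If treatment means radiotherapy. With surgery 4–6 weeks after radiotherapy, 12 months after radiotherapy falls 4–6 weeks before 12 months after surgery. If treatment includes surgery, C becomes a failure under the Primary objective; A, B and D are unchanged.

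A separates the Primary objective from the toxicity section without any help from the abstract or from 'and/or'.

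**3. The plan's own figure**

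Inputs from the statistical section: two-sided 95% Agresti–Coull interval per arm, assumed proportion 0.90, lower limit not below 0.75, n = 32 per arm.

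With z = 1.96 and z² = 3.84:

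- ñ = n + z² = 32 + 3.84 = 35.84
- p̃ = (x + z²/2)/ñ
- lower limit = p̃ − z·√(p̃(1 − p̃)/ñ)

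The expected count is 0.90 × 32 = 28.8, so the nearest whole number is x = 29:

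- p̃ = (29 + 1.92)/35.84 = 0.863
- lower limit = 0.863 − 1.96·√(0.863 × 0.137/35.84) = 0.750

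The stated n = 32 is reproduced.

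**4. Sensitivity to reclassification**

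| Successes of 32 | Lower limit |
|---|---|
| 29 | 0.750 |
| 28 | 0.713 |
| 27 | 0.678 |
| 26 | 0.643 |

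One patient classified the other way costs 0.750 − 0.713 = 0.037 on the lower limit.

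**The case against.** The strongest reply is that there are fewer definitions than four. Only the Primary objective section uses the language of a definition. The statistical section repeats it with one loose connective in a planning sentence. The abstract is a summary, and its discontinuation rule differs from the toxicity section's only where the cause is uncertain. The formal definition most naturally covers toxicity during radiotherapy too, and if treatment includes surgery the end dates agree. Much of this stands: 'and/or' is probably a drafting slip, and the difference in window end depends on reading treatment as radiotherapy. What it does not remove is the conflict over discontinuation between the Primary objective and toxicity sections, or the fact that 'and/or' stands in the sentence that fixes the 0.90.

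A reader might infer more than the article supports:

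- **That the trial's conclusion turns on 29 versus 28 successes.** It does not. The 0.75 is a precision goal used to choose n, all analyses are declared descriptive, and no go/no-go rule is attached to the observed interval.
- **That about five patients per arm are at stake**, from the photon figure of about 15% grade 3 or higher toxicity before surgery (0.15 × 32 = 4.8). That shift arises only if the abstract's literal window governs, and it applies a photon rate to particle arms planned at 0.90. The same sentence gives 33% after surgery. Applied consistently, that leaves about 32 − 0.33 × 32 = 21 successes in the abstract's window, so a starting point of 29 cannot be combined with it. The overlap between events before and after surgery is not given.
- **That the definition will be picked after unblinded data are seen.** The article does not state whether the trial is blinded, and the full protocol (version 2.2, under Trial status) is not shown and may settle the wording.

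Detailed handling of patients who are never resected may also stand in the full protocol, so its absence is not held against the article.

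**Conclusion.** The inconsistency is real and concerns the primary endpoint. It has three parts: which discontinuations count, 'and' against 'and/or', and the window. The first two need no assumption beyond the text. The 4–6 week difference in the end of the window rests on treatment meaning radiotherapy, as Regular study end indicates. The loss of events before surgery rests on reading the abstract literally.

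The number of patients affected cannot be derived from the article. The supportable size is the sensitivity figure: one patient in 32 moves the lower limit from 0.750 to 0.713, against the planning target of 0.75. The article also gives no basis for preferring the toxicity section's discontinuation rule to that of the formal definition, or the reverse. The passages have to be reconciled.

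**What to change.** State one definition and use it unchanged in the abstract, Primary objective, toxicity and statistical sections, including for the assumed 0.90.

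1. Replace 'and/or' in the sample-size sentence with 'and', as in the Primary objective and toxicity sections.
2. Give the window an explicit start at the first fraction, as the toxicity section already does, and one explicit end anchor that also yields an end date for a patient who is not resected. Align the abstract with it.
3. Have the sponsor reconcile the discontinuation rule of the Primary objective and statistical sections with that of the toxicity section before the data are analysed. Report the rule not chosen as a sensitivity analysis.

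The cost is an amendment to the wording of the primary endpoint in a running trial (recruitment began on April 30, 2019). No new data collection is needed: toxicity is already recorded from radiotherapy onward, and follow-up runs to 12 months after surgery.

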### Secondary objectives

Assessment of local control (LC) and local progression-free survival (LPFS) and disease-free survival (DFS). Further objectives are overall survival (OS) from the start of treatment until death or censoring and quality of life (QoL) using the EORTC-QLQ30 questionnaire.

### Study design

The study is a parallel-group prospective clinical phase II trial of patients with retroperitoneal sarcoma, randomized to one of the two treatment arms (arm A: proton therapy, arm B: carbon ion therapy). A total dose of 39 Gy (RBE) in 13 fractions to the PTV (see target definition below) will be given in both arms. The accrual period of this trial will take approx. 4 years with a follow-up time of 12 months for each patient. Patients matching the eligibility criteria and willing to participate with written informed consent are registered at Heidelberg University Hospital (Fig. 1).

### Inclusion criteria

i)Histological confirmation of non-metastatic retroperitoneal soft tissue sarcoma, which is resectable or marginally resectableii)Karnofsky performance status ≥ 70%iii)Patients age above or equal 18iv)Written informed consent

### Exclusion criteria

i)Distant and/or lymph node metastasesii)Desmoid tumors, gastrointestinal stromal tumor (GIST), peritoneal sarcomatosisiii)Metal implants at the level of the tumor that could influence treatment planningiv)Inability of the patient to lie quietly for at least 20 min (e.g., due to pain)v)Prior radiotherapy to the abdominopelvic cavityvi)Simultaneous participation in another trial that could influence the results of the studyvii)Active medical implants without treatment approval at the time of ion irradiation (e.g., cardiac pacemaker, defibrillator)viii)Pregnancy

### Treatment planning and target volume delineation

Examinations for treatment planning consist of a CT scan (3-mm slice thickness) in treatment position and a MRI for 3D image correlation. The delineation of the retroperitoneal soft tissue sarcoma requires a T1-weighted post-gadolinium sequence.

Gross tumor volume (GTV) includes the gross tumor based on CT and MRI imaging. The clinical target volume (CTV) is defined as GTV plus surrounding areas at risk for containing microscopic disease. The CTV includes the GTV with a margin of 2 cm. The CTV margins may be smaller if the GTV is adjacent to the critical normal organs like the small bowel. The planning target volume (PTV) includes the CTV with an additional margin of 5 mm in the anterior–posterior direction and 7 mm in the lateral direction to compensate set-up variability. The overlap of PTV and the rectum or intestine is defined as PTV-rectum or PTV-intestine.

### Proton/carbon ion therapy

Treatment will be administered on an outpatient basis at the Heidelberg Ion-Beam Therapy Center (HIT) exclusively in active raster scanning technique [11, 12]. Apart from the standard supportive treatment, no other treatment will be administered in parallel to radiotherapy. Treatment planning is realized using a treatment planning system (TPS Siemens) that enables conventional and biological optimization. After inverse planning, proton and carbon ion treatment is given in active beam application (raster scanning method).

### Dose prescription and constraints of critical organs at risk

Ninety-five percent of the PTV should obtain the dose of 39 Gy (RBE) in 13 fractions (5–6 fractions per week). The rectum, bladder, intestine, and kidney will be defined as organs at risk depending on the exact tumor localization. It is assumed that the *α*/*β* value of soft tissue sarcoma is < 10; a consistent value cannot be found in literature. The equivalent photon dose in 2 Gy fractions (EQD2) is in the range of 48.8–42.2 Gy for a *α*/*β* = 2–10. The maximal dose for PTV-intestine and PTV-rectum is 39 Gy (RBE) (100% isodose). The EQD2 is 45.5 Gy for the intestine (*α*/*β* = 4.0 Gy) and 45.6 Gy (*α*/*β* = 3.9 Gy). This dose will be allowed to a small volume only and not circumferentially. The maximum dose for the myelon and cauda equina is 37.0 Gy (RBE) (95% isodose), and the EQD2 is 44.9 Gy. If no nephrectomy is planned, two-thirds of the kidney volume should receive less than 26.5 Gy (RBE) (68% isodose) and one-third should receive less than 33.5 Gy (86% isodose). The Quantitative Analyses of Normal Tissue Effects in the Clinic (QUANTEC) criteria for the rectum, bladder, and the further bowel will be followed (V50 < 50%, V60 < 35%, V65 < 25%, V70 < 20%, and V75 < 15%).

### Toxicity, safety, and quality of life

Toxicity will be evaluated according to International Common Terminology Criteria for Adverse Events (CTCAE) version 5.0 for toxicity (case report forms) and adverse event reporting including the results of clinical examinations as well as imaging studies (MRI or CT). At enrollment, each patient will pass a baseline clinical examination. During treatment, the patient is monitored continuously and acute adverse events will be documented weekly and at the end of treatment. Three weeks after the end of radiotherapy, the patient will receive an MRI, and the surgery is planned 4–6 weeks after RT. The further follow-up presentations are 6 weeks and 3, 6, 9, and 12 months after the tumor resection and include all imaging studies (CT/MRI) (Table 1). The criteria for feasibility and safety are fulfilled, if no grade 3 or higher toxicity has occurred from the start of irradiation until 12 months after surgery, and if the therapy was not canceled due to any reason (unless clearly not treatment related).

**Table 1 Tab1:** Time flow of procedures and examinations

	Study inclusion	Prior to RT	During RT	At the end of RT	3 weeks after RT	OP: 4–6 weeks after RT	6 weeks after RT	3 months after OP	6 months after OP	9 months after OP	12 months after OP
Inclusion and exclusion criteria	x										
Informed consent	x										
Medical history	x		x	x	x		x	x	x	x	x
Evaluation of symptoms and toxicity	x		x	x	x		x	x	x	x	x
Radiotherapy			x								
Resection						x					
MRI abdomen/pelvis		x			x			x	x	x	x
CT thorax		x						x	x	x	x
Quality of life (QLQ-C30)		x			x			x			x

Quality of life (QoL) will be assessed by the means of the EORTC QLQ-C30 questionnaires. Those will be filled out by the patient before treatment, 3 weeks after the end of RT, 6 months after surgery, and at the end of the observation interval of 12 months. The evaluation will be carried out after the complete acquisition of data. Changes in QoL will be determined comparing the results before and after radiotherapy as well as the difference before and after surgery. QoL will be compared between the two arms of the study after the end of radiation and at the end of the observation interval.

